### Intervention

The VaLiANT program is a manualized group intervention that concurrently targets cognition and emotion by integrating cognitive rehabilitation and ACT techniques to improve engagement in valued activities following ABI. The program consists of eight 2-h group sessions delivered either in-person or *via* telehealth during periods of COVID-19 restrictions, with group sizes ranging from three to eight participants. The intervention was developed by the authors, drawing on their clinical and research expertise, however evidence-based ACT and cognitive rehabilitation techniques and materials were adapted from existing manualized treatments to supplement the new content (46, 59–62). Group delivery was chosen due to a number of factors: 1) the cost-effectiveness compared to individual treatment, 2) the additional benefit of group discussion and the sharing of ideas for particular topics e.g., strategies to manage particular difficulties following ABI, and 3) to address social isolation and provide access to other individuals with shared experience. A number of small revisions were made to the manual and treatment delivery following completion of the Phase I study (55): 1) additional scaffolding was added in Session 2 to assist participants with linking their values to behavior, 2) a mindfulness exercise was included in every session (previously was in most but not all sessions), and 3) email reminders for the homework activities were sent to participants at the end of each calendar week. The treatment manual and resources will be published following completion of the trial. For more information on the intervention content and additional modifications made due to COVID-19, please see Tables 1, 2.

**Table 1 T1:** TIDieR checklist describing the Valued Living After Neurological Trauma intervention and telehealth modifications.

**Item**	**Telehealth modification**
*1. Name* Valued Living After Neurological Trauma (VaLiANT)	

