### Randomization and Blinding

Randomization is performed by a researcher independent from the study using an online generator known as Research Randomizer (https://www.randomizer.org). Eligible participants are randomly assigned to the intervention condition or control condition with an allocation ratio of 2:1 (Intervention: Control). This allocation ratio was selected to optimize recruitment rates and maximize the number of people experiencing the intervention to allow for exploration of treatment dimensions and predictors of outcome (84, 85). Randomly permuted block sizes of 3, 6, or 9 are used to ensure a balanced allocation ratio. Group allocation is concealed, either in sequentially numbered sealed opaque envelopes (pre-COVID) or electronically *via* sequentially numbered word-documents uploaded to a protected cloud-sharing platform (post-COVID), which are opened at the end of the baseline (T1) assessment. The outcome assessors at T2 and T3 are research assistants blinded to condition allocation. Participants are reminded to not disclose their allocation during assessments, and all instances of unblinding are recorded. If unblinding occurs during a T2 assessment, then a different blinded research assistant conducts that participant's T3 assessment.

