### Procedure

The VaLiANT group is planned to run quarterly with an associated participant intake period prior to commencement of each group. Potential participants undergo screening to ensure eligibility before informed consent is obtained. For each intake, all eligible participants attend an initial baseline assessment (T1) which includes all baseline sample characterization measures and primary and secondary outcome measures. Randomization occurs immediately following the T1 assessment. In addition to their usual care, participants in the treatment condition then attend the 8-week VaLiANT group program at the La Trobe University Psychology Clinic, or *via* telehealth (Zoom videoconferencing) during periods of COVID-19 restrictions, while control participants undergo treatment-as-usual (i.e., their usual care). Participation in other treatment during the trial is documented, including the frequency and type of treatment. VaLiANT group sessions are facilitated by an experienced clinical neuropsychologist with assistance from two trainee psychologists. All sessions are video-recorded. Outcome assessments occur within 1–2 weeks following the intervention/waiting period (T2), and at an 8-week follow-up (T3). All assessments take roughly 90 min and are administered by assessors blinded to condition allocation. Assessments are conducted at the La Trobe University Psychology Clinic or in participants' homes if preferable. During periods where COVID-19 restrictions apply, assessments are conducted over Zoom videoconferencing.

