### Sample Size Calculation

A power analysis was conducted using 5,000 simulations within the SimR package for R (86) to determine if the maximum possible sample size during the data collection period (*N* = 64) was sufficient for the statistical analyses. A previous evaluation of an ACT-based intervention following stroke reached a moderate group-by-time effect (η2 = 0.07) on the Warwick and Edinburgh Mental Wellbeing Scale (51). Accordingly, a minimum sample of 52 participants is required to achieve statistical power for a linear mixed-effect model with a 2 (group) x 3 (time) design (80% power, α = 0.05). Allowing for an attrition rate of 10%, an N of 58 is adequate to perform the primary analyses.

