### Statistical Analysis

Main analyses will follow an intention-to-treat approach. Little's missing completely at random (MCAR) analysis will be conducted to determine if data are MCAR (87). If <5% of data is MCAR, the appropriate data imputation technique will be employed to deal with missing values [likely Markov chain Monte Carlo method; (88)]. Univariate outliers (z +/− 1.96 SD) will be adjusted using a winsorising solution (89). Univariate checks of normality (skewness > +/− 2.58 SD) will be conducted, and variables that violate the criterion will be corrected to normal using appropriate data transformation (90). Primary and secondary outcomes will be analyzed with linear mixed models, with fixed effects of time and group, and participants modeled as random effects. The estimated marginal means from the model will be used to calculate effect sizes (Cohen's *d*) to illustrate change in both between group and timepoint contrasts. The results of the fixed effects estimates for the main effects and interaction terms will be presented as standardized *B* values and all analyses will use a two-sided alpha level of 0.05. These analyses will be conducted using JASP (91). Finally, as an adjunct to the linear mixed models, the Crawford and Howell measure of reliable change (92), which is suitable for serial testing, will be calculated for the primary outcome (93). The proportion of participants achieving reliable change in each group at both time-points will then be compared with 2 × 2 Chi square tests of independence.

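### The mixed model has participants as its only random effect, although the intervention arm alone is treated in therapy groups of 3 to 8; with any positive within-group correlation the arm contrast is reported too precisely, and no therapy-group variance is estimated

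*Protocol article*

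**What the plan says.** The Statistical Analysis section of the protocol article gives one model for primary and secondary outcomes: "linear mixed models, with fixed effects of time and group, and participants modeled as random effects". That group means trial arm is clear from the Sample Size Calculation section, which describes a "linear mixed-effect model with a 2 (group) x 3 (time) design". Neither section has a term for therapy group or intake, and none appears elsewhere in the article.

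The Intervention section describes eight two-hour sessions delivered "with group sizes ranging from three to eight participants", and lists among the reasons for group delivery "the additional benefit of group discussion and the sharing of ideas". Table 1 adds that most activities are group discussions (item 4), that trainee co-facilitators each assist with only one or two groups (item 5), and that emphasis shifts with the barriers a particular group reports (item 9). The Procedure section says that intervention participants attend the group program "while control participants undergo treatment-as-usual (i.e., their usual care"), so the control arm has no therapy groups.

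The first aim, at the end of the Introduction, includes determining parameter estimates for a definitive Phase III trial.

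**The concern.** A participant random effect accounts for the correlation between one person's three assessments. It does not account for correlation between different people who sat through the same eight sessions. After treatment starts, members of one therapy group share co-facilitators, discussion, tailored content and mode of delivery, so their T2 and T3 scores may be correlated. Controls have no such structure, and T1 precedes randomisation and therefore treatment. The result is clustering in one arm at two of the three time points.

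If that correlation is positive, the variance of the intervention-arm mean is larger than the model assumes. The interval for the arm contrast is then too narrow and the test rejects too often under the null. Separately, the model has no parameter for between-group variation, which is one of the quantities a later group-therapy trial would want to know.

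**Working it through.** **The plan's own figures.** The article states "80% power, α = 0.05", a minimum of 52 participants and 10% attrition. 52 / (1 − 0.10) = 57.8, which rounds up to the stated 58. The 52 itself came from simulation whose variance components and mean pattern are not given, so it cannot be recomputed. It is used here only as the number analysed.

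**Inputs**
- Allocation: the Randomization and Blinding section assigns participants "with an allocation ratio of 2:1 (Intervention: Control"), so 52 splits into about n_T = 35 and n_C = 17.
- Therapy-group size m: 3 to 8 (Intervention section); 5 is taken as a middle value.
- Alpha: "all analyses will use a two-sided alpha level of 0.05".
- ICC: not in the documents. Assumed range 0.01 to 0.10, on the scale of the contrast being tested.

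**Formulas** (outcome variance set to 1)
- Design effect in the intervention arm only: DE = 1 + (m − 1) × ICC
- True variance of the arm difference: DE/n_T + 1/n_C
- Variance that ignores therapy group: 1/35 + 1/17 = 0.08739
- k = true variance / naive variance; standard-error ratio = √k
- Actual two-sided type I error = 2 × P(t > 2.009/√k), with 35 + 17 − 2 = 50 degrees of freedom

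**Worked case, m = 5, ICC 0.05.** DE = 1 + 4 × 0.05 = 1.20. True variance = 1.20/35 + 1/17 = 0.09311. k = 0.09311/0.08739 = 1.065. √k = 1.032. Type I error = 5.7%.

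| m | ICC | DE | k | SE ratio | Type I error |
|---|---|---|---|---|---|
| 3 | 0.01 | 1.02 | 1.007 | 1.003 | 5.1% |
| 3 | 0.05 | 1.10 | 1.033 | 1.016 | 5.4% |
| 3 | 0.10 | 1.20 | 1.065 | 1.032 | 5.7% |
| 5 | 0.01 | 1.04 | 1.013 | 1.007 | 5.1% |
| 5 | 0.05 | 1.20 | 1.065 | 1.032 | 5.7% |
| 5 | 0.10 | 1.40 | 1.131 | 1.063 | 6.5% |
| 8 | 0.01 | 1.07 | 1.023 | 1.011 | 5.3% |
| 8 | 0.05 | 1.35 | 1.114 | 1.056 | 6.3% |
| 8 | 0.10 | 1.70 | 1.229 | 1.109 | 7.6% |

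The ratio k says how much larger the true variance is. The shortfall of the naive figure is 1 − 1/k for the variance and 1 − 1/√k for the standard error. For k = 1.065, 1.131 and 1.229, the variance is understated by 6.1%, 11.6% and 18.6%, and the standard error by about 3%, 6% and 10%.

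**Simulation check.** The closed form treats one contrast, not the full three-time model. Simulating that two-arm contrast under the null (20,000 runs, 39 versus 19) gave type I error of about 5.0% at ICC 0 and 5.6% to 7.9% across ICC 0.05 to 0.10 and m = 3 to 8. The excess therefore comes from clustering.

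**How well the group variance could be estimated.** Between 35/8 = 4.4 groups (35 treated, groups of 8) and 43/3 = 14.3 groups (43 of the maximum 64 treated, groups of 3) would be formed, so roughly 5 to 14. In a balanced one-way layout with J groups, the between-group variance is estimated at or below zero with probability P(F < 1/[1 + m × ICC/(1 − ICC)]), with J − 1 and J(m − 1) degrees of freedom.
- 8 groups of 5: 1 + 5 × 0.05/0.95 = 1.263, giving 40% at ICC 0.05; 28% at ICC 0.10.
- 12 groups of 3: 1 + 3 × 0.05/0.95 = 1.158, giving about 42% at ICC 0.05.
- With 8 groups of 5 and an observed F of 1.263, the 95% interval for the ICC runs from about −0.12 to 0.47.

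**The case against.** The strongest reply is that the harm is conditional and small. The documents contain no ICC. At 0.01 the effect is negligible, and in the middle case (groups of 5, ICC 0.05) the standard error is only about 3% too small. This is a Phase II pilot looking for signals of efficacy, and a type I error of 5.7% instead of 5% would not overturn its conclusions. All of this stands, and it limits the weight of the point. A reader might infer that the intervals are certainly too narrow and that the false-positive rate certainly exceeds 5%. The documents do not support that without a positive ICC; they only make one plausible.

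A second reply is that the remedy delivers less than it seems to. With so few groups the variance is often estimated at zero, in which case the extended model largely reverts to the planned one. This also stands. A reader might infer that the trial would yield an ICC fit to size Phase III, or that omitting it contradicts the first aim. Neither follows: the estimate would be too imprecise, and the aim refers to parameter estimates without naming an ICC.

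A third reply is that this is a condensed article and a fuller analysis plan may exist. That carries less weight, because the article does not leave the random effects open. It states them, and therapy group is not among them.

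**Conclusion.** The point holds in conditional form. The stated model ignores the partial nesting that the protocol's own delivery format creates. If the within-group ICC is positive, the arm contrast is reported too precisely. Over an assumed ICC of 0.01 to 0.10, groups of 3 to 8 and 35 versus 17 analysed, the true standard error is about 1.003 to 1.11 times the model's, and type I error about 5.1% to 7.6%. These sizes rest on the assumed ICC and on a simplified contrast with equal group sizes. Whatever the true ICC, the model reports no therapy-group variance component, although the trial is meant to inform Phase III.

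This should be fixed before analysis, but it is not a defect that invalidates a Phase II pilot. Nor does it show the planned 52 or 58 to be wrong: the inputs behind 52 are not given and the ICC is unknown.

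**What to change.** In the Statistical Analysis section, add a random effect for therapy group that applies only to intervention-arm observations at T2 and T3, and is zero for controls and at T1. Use Satterthwaite or Kenward-Roger degrees of freedom. Report the therapy-group ICC with its interval, and state that it will not by itself determine the Phase III sample size. If JASP cannot fit an arm-specific random effect, fit the model in R, which the trial already uses for its power simulation.

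The cost is a few sentences, a therapy-group identifier in the data set and at least one more variance parameter. Recruitment, treatment and assessments are unaffected. The interval for the arm contrast widens slightly. With roughly 5 to 14 groups the ICC will be very imprecise and often estimated at zero, so type I error is only partly protected.

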### Protocol Amendments Due to COVID-19

The COVID-19 pandemic has resulted in a number of essential methodological changes to the original study protocol. The trial commenced in August 2019, and then in March 2020 it was paused for 6-months after the onset of the pandemic, given that restrictions prevented in-person assessments and intervention delivery. To allow the trial to continue, the research team redeveloped the study protocol for telehealth delivery on Zoom. To allow for outcome assessments to be conducted *via* telehealth, data collection measures have been moved from Qualtrics to REDCap, the randomization schedule has shifted from opaque envelopes to sequentially numbered word-documents uploaded to a cloud-sharing platform, and the paper-and-pencil Trail Making Test has been substituted with the oral version for telehealth baseline assessments. A telehealth version of the VaLiANT intervention was also developed (see Table 1). For analyses, telehealth delivery will be treated as a substitution for in-person delivery rather than as a separate treatment arm. In-person delivery remains the preferred modality and will be utilized where possible. Changes have been made to the inclusion criteria such that participants are required to be able to attend assessments and the intervention both in-person and *via* telehealth, to allow flexibility with changing restrictions.

In addition, a number of other non-essential modifications have been made following the opportunity to reflect on the trial design during the trial's pause in 2020, and further evidence accumulated during that period. In weighing up whether to introduce these changes after trial commencement, the research team considered the fact that this is a feasibility Phase II trial and therefore opted to make changes to optimize trial design and better inform a future Phase III trial. Initially, randomization occurred in randomly permuted block sizes of 6. However, it was possible for the baseline assessor to deduce the final participant's allocation in one block based on previous allocations. As such, varying block sizes (3, 6, or 9) were introduced to maximize blinding of the baseline assessor in future assessments. The Community Integration Questionnaire was updated to the revised version which includes an additional electronic social networking scale, relevant in the context of social distancing requirements. The 26-item World Health Organization Quality of Life scale (WHOQOL-BREF) and the Head Injury Semantic Differential Scale – III (HISDS-III) were included as additional outcome measures to provide more comprehensive measurement of quality of life and psychological adjustment. Finally, the Valued Living Questionnaire (VLQ) was replaced with an adapted version (VLQ-CS) following identification of validity issues with the original measures due to frequent comprehension errors made by those with ABI^2^. All modifications occurred during the pause in data collection (March – September 2020) with the exception of changes to the Valued Living Questionnaire which occurred in September 2019.

## Discussion

There is a recognized need for trials evaluating complex, multi-domain, person-centered interventions post-ABI that aim to improve rehabilitation outcomes beyond injury-related impairments (e.g., cognitive and mood changes) by also targeting overall adjustment to injury, meaningful participation, and quality of life (33). While a number of complex interventions have integrated cognitive rehabilitation and psychological therapy with subsequent positive long-term effects, these interventions are lengthy and require high treatment dosage which limits their implementation into routine practice. The proposed RCT aims to build on our Phase I findings (55) by evaluating the efficacy, feasibility, and acceptability of the 8-week VaLiANT group program against a treatment-as-usual waitlist control.

The study has several strengths. Many aspects of the current trial design were piloted and found to be feasible in the previous Phase I study (e.g., recruitment rates, outcome assessment completion rates). The inclusion criteria for the study are broad and include multiple forms of ABI in comparison to many intervention studies which focus on a single cohort (e.g., stroke). It is therefore anticipated that the sample will be fairly heterogeneous, supporting generalization of the study findings to the broader ABI community and implementation into ABI rehabilitation services (which are rarely devoted to a single cohort), while potentially also allowing for greater exploration of predictors of treatment outcome depending on the sample size. Additionally, the intervention was developed by a multi-disciplinary team based on current evidence (including existing manualized treatment approaches). The intervention includes specific adaptations to meet the needs of those with ABI, it can be delivered both in-person and *via* telehealth aiding flexibility, and it is group-based which may be more cost-effective than individual therapy.

Several limitations are also acknowledged. The study has been conducted during the COVID-19 pandemic in Melbourne, Australia which has been subject to multiple extended and rolling lockdowns throughout the study period. Study outcomes may be impacted during periods of restriction due to limited opportunities for intervention-related behavior change and the overall negative impact on mood and wellbeing. Additionally, there may be rapid improvements in both study conditions when lockdowns or restrictions are eased. The pandemic has also necessitated a number of changes to the study design and methodology. In particular, the variable modality of intervention delivery between participants (i.e., in-person, telehealth, or blended) may impact intervention outcome. The associated change in inclusion criteria, which requires participants to have both in-person and telehealth capacity, may also lead to a restricted sample by limiting the intervention to higher-functioning individuals. The study is also limited to English speaking individuals with sufficient cognitive and language capacity to complete the outcome assessments and participate in the group intervention, which may further limit the generalizability of findings, particularly to those with significant aphasia.

This study will extend current knowledge on the utility of complex interventions and will add to the growing body of evidence investigating the role of valued living as an important treatment target following ABI. The study findings will also add to recent evidence supporting the adaptation of ACT for those with ABI. Given that previous investigations have focused on purely ACT-based interventions without a cognitive rehabilitation component, this study will demonstrate the utility of incorporating ACT principles within a more holistic intervention framework. Finally, study findings will help determine the feasibility and implementation of a definitive Phase III RCT.

## Data Availability Statement

The original contributions presented in the study are included in the article/supplementary material, further inquiries can be directed to the corresponding author.

## Ethics Statement

The studies involving human participants were reviewed and approved by La Trobe University Human Research Ethics Committee. The patients/participants provided their written informed consent to participate in this study.

